### Outcome

The primary outcome will be the total motor domain score of FIM at hospital discharge. The FIM motor score at hospital discharge was selected as the primary outcome because it represents the earliest clinically stable time point at which the cumulative effects of ICU-based interventions can be meaningfully assessed. FIM at ICU discharge may be influenced by non-clinical factors such as bed availability and transfer policies, and may underestimate functional recovery due to ongoing critical illness and sedation effects. In contrast, longer-term follow-up after discharge is more susceptible to loss to follow-up and confounding by post-ICU rehabilitation and social factors. Therefore, assessment at hospital discharge was considered the most appropriate balance between clinical relevance, feasibility, and internal validity.

Secondary outcomes and their assessment time points will be as follows:At ICU discharge: Functional Status Score for the ICU [31], Medical Research Council (MRC) score, and ICU length of stay.At 14 days after ICU discharge: FIM motor, cognitive subscale of FIM (FIM cog), Mini-Mental State Examination (MMSE), body composition parameters, MRC score, and Brief Pain Inventory (BPI).At hospital discharge: MRC score, FIM cog, body composition parameters, BPI, length of hospital stay, and mortality.At 60 days after hospital discharge: FIM motor score, MRC score, FIM cog, MMSE score, body composition parameters, and BPI.

Follow-up at 60 days post-discharge will be conducted during an outpatient visit scheduled at the time of discharge. For patients who die or cannot be assessed owing to severe consciousness disturbance, the FIM motor and FIM cog will be recorded at their minimum values (13 and 5, respectively), the MRC score will be assigned as 0, and the BPI will be recorded as missing. For patients who die before hospital discharge, FIM scores will be assigned as the minimum possible values (motor score 13 and cognitive score 5). This approach reflects that death represents the worst possible functional outcome and ensures that mortality is appropriately incorporated into the analysis of functional recovery rather than treated as missing data.

Safety outcomes will include serum creatinine level at hospital discharge, maximum blood urea nitrogen level during the intervention, mean insulin use, and maximum blood glucose levels. In addition, mobilization-related safety outcomes will include accidental removal of tubes or devices, the number of mobilization sessions discontinued, and reasons for discontinuation (respiratory, circulatory, neurological, fatigue, or other causes). The schedule of enrolment, interventions, and assessments follows the SPIRIT 2025 guidelines (Fig. 3).

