### Statistical analyses

After data collection is complete, continuous variables will be presented as mean ± SD or as median with interquartile range (IQR), and categorical variables as numbers with percentages. Baseline characteristics and study outcomes will be compared between groups using the Student’s t-test or Mann–Whitney *U* test for continuous variables, and the chi-square test or Fisher’s exact test for categorical variables. All outcome analyses will be conducted according to the intention-to-treat principle.

The primary analysis will compare outcomes between groups according to the intention-to-treat principle.

As a sensitivity analysis, analysis of covariance (ANCOVA) will be performed to explore the robustness of the primary findings to variability in intervention implementation. As the actual duration of high-protein nutrition and high-intensity mobilization may vary among participants despite randomization, these variables will be included as covariates to account for differences in intervention exposure rather than to adjust the primary treatment effect.

Covariates included in the ANCOVA will be pre-specified based on clinical relevance and trial design considerations, not selected in a data-driven manner. Importantly, these analyses are intended as exploratory sensitivity analyses to aid interpretation of the results and will not replace the primary intention-to-treat comparisons.

Furthermore, sensitivity analyses will be performed with adjustment for the presence of acute kidney injury and use of renal replacement therapy (RRT).

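### No death rule is given for ICU and hospital length of stay, so if deaths come early, the arm with more deaths can look better on stay

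*Protocol article*

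**What the plan says.** The Abstract names ICU stay and hospital stay among the secondary outcomes. The Outcome section repeats them: at ICU discharge, "Functional Status Score for the ICU [31], Medical Research Council (MRC) score, and ICU length of stay"; at hospital discharge, "MRC score, FIM cog, body composition parameters, BPI, length of hospital stay, and mortality". Mortality is thus a separate item at the same time point as hospital stay.

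The Statistical analyses section gives one rule for all continuous outcomes. The sentence that begins "Baseline characteristics and study outcomes will be compared between groups using the" assigns them a t-test or a Mann–Whitney test, and assigns contingency-table tests to categorical outcomes. The population is equally general: "All outcome analyses will be conducted according to the intention-to-treat principle".

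The Outcome section sets values for patients who die before hospital discharge: "FIM scores will be assigned as the minimum possible values (motor score 13 and cognitive score 5"). For patients who die or cannot be assessed, "the MRC score will be assigned as 0, and the BPI will be recorded as missing". The reason given is that this "ensures that mortality is appropriately incorporated into the analysis of functional recovery rather than treated as missing data". Neither length of stay appears in these rules. The article names no time-to-discharge, competing-risk, worst-rank or survivors-only analysis for stay.

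**The concern.** Length of stay ends either by discharge alive or by death, and a short stay means opposite things in the two cases. If both are entered as a number of days, an early death counts as a short stay, which readers normally take as favourable.

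This matters here because the protocol itself allows for a mortality difference. Its Background cites evidence that higher protein may be harmful in some settings and describes a U-shaped relation with outcomes such as mortality. Its Discussion notes possible harm in severe acute kidney injury. The population is mechanically ventilated and may include patients on ECMO. If high protein led to more early deaths, the two stay comparisons would tend to favour high protein, so a harm signal would appear as an apparent benefit on two secondary outcomes named in the Abstract.

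**Working it through.** **What the documents supply.** They give 90 patients at 1:1, so 45 per arm, two-sided testing at 0.05, and the tests and population above. They give no mortality, no timing of death and no stay distribution. There is no stated figure on stay to reproduce, and every magnitude below rests on assumed inputs.

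**Step 1: which value does a death receive?** This has to be inferred. Intention to treat keeps deaths in the comparison. Death values are set for FIM, MRC and BPI and not for stay. Nothing says that the stay of a patient who died is missing, and ICU stay is itself listed as a predictor in the imputation model, which suggests that it is treated as observed. The natural reading is the observed stay up to death.

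**Step 2: direction and size in closed form.** Let survivors stay S days, deaths occur at D days, and mortality be m.

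Mean stay = (1 − m)·S + m·D

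With S = 30 and D = 12:
- m = 0.20: 0.80 × 30 + 0.20 × 12 = 24.0 + 2.4 = 26.4 days
- m = 0.30: 0.70 × 30 + 0.30 × 12 = 21.0 + 3.6 = 24.6 days
- Difference: 1.8 days in favour of the arm with more deaths, although survivors' stay is the same in both.

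In general the spurious gain is (difference in m) × (S − D), so its sign depends on when deaths occur. For a mortality difference of 0.10 and S = 30:

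| Deaths at day | Apparent gain for the arm with more deaths |
|---|---|
| 8 | 0.10 × 22 = 2.2 days |
| 12 | 0.10 × 18 = 1.8 days |
| 30 | 0 |
| 45 | 0.10 × (−15) = −1.5 days (looks worse) |

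**Step 3: simulation with skewed stays.** Assumptions: 45 per arm; survivors' stay lognormal with median 30 days and log-SD 0.7, identical in both arms; stay of deaths lognormal with median 8 days and log-SD 0.7; 20% mortality in the comparison arm; 4,000 replicates. The last three columns give the share of trials in which the arm with more deaths is significantly better on stay.

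| Mortality | Mean difference in medians (days) | Mann–Whitney | t-test | Deaths ranked longest |
|---|---|---|---|---|
| 20% v 20% | 0.0 | 2.5% | 2.2% | 2.2% |
| 20% v 30% | −3.1 | 9.7% | 7.7% | 0.3% |
| 20% v 35% | −4.6 | 17.1% | 11.4% | 0.0% |
| 20% v 40% | −6.0 | 25.5% | 16.4% | 0.0% |

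In the first row mortality is equal, so the shares refer to one designated arm.

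Check on the simulation: the lognormal means are 30 × exp(0.7²/2) = 38.3 days for survivors and 8 × exp(0.7²/2) = 10.2 days for deaths. A mortality difference of 0.10 should shift the mean by 0.10 × 28.1 = 2.8 days; the simulated shift was 2.9.

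**Step 4: sensitivity to timing.** At 20% v 35% mortality, with deaths at median day 30, the difference in medians is 0.0 days and 2.6% of trials favour the arm with more deaths by Mann–Whitney. With deaths at median day 45, that arm's stay is 1.9 days longer and the share is 0.9%.

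**The case against.** The strongest reply is that the article never says what stay a deceased patient is given. The Mann–Whitney test as stated could accommodate deaths ranked longest, and such a rule could sit in a fuller document. The step is indeed an inference. But the article fixes a test and a population for these outcomes and sets death values for others in the same section, so observed stay is the reading that an analyst would most naturally follow.

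The second reply is size. Under the lognormal assumption the survivors' SD is about 30 days, so the standard error of a mean difference is about 30.5 × √(2/45) = 6.4 days, and 1.8 days is about 0.3 of that. At 20% v 30% mortality, about 90% of simulated trials show no significant advantage for the arm with more deaths. This stands: the expected distortion is modest unless the mortality difference is large.

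Third, mortality is reported separately, so an imbalance would be visible. That helps a careful reader but corrects neither the stay estimate nor its p-value. Observed stay in everyone randomised is also a legitimate measure of resource use, although the article does not present it as that.

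Three stronger readings might be inferred and are not supported:
- *The plan contradicts its own view of death.* The Outcome section calls death the worst functional outcome and limits the rule to functional recovery. Stay is not a functional score, so nothing is contradicted.
- *Duration of ventilation has the same defect.* Data collection lists it as treatment-related data, and it is not among the outcomes.
- *The direction of benefit is always reversed.* It depends on timing, as shown above. Patients with a life expectancy under 7 days are also excluded, which should reduce very early deaths without ruling them out.

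**Conclusion.** The point holds in limited form. ICU and hospital stay are to be compared by simple tests in all randomised patients with no stated rule for deaths. If deaths enter with their observed stay and fall earlier than typical discharge, the arm with more deaths tends to look better. With assumed inputs the spurious gain is 1.8 days in the simple example. In the simulation, the chance of a significant result favouring the arm with more deaths rises from about 2.5% to between 9.7% and 25.5% by Mann–Whitney for mortality differences of 10 to 20 points. The bias is absent if deaths occur around the survivors' median stay and changes sign if they occur later. Only these two secondary outcomes are concerned. The primary FIM motor comparison has its own death rule and is not affected by this point.

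**What to change.** State how death is handled for both stays, by one of two routes:

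1. Analyse time to discharge alive with death as a competing event, reporting cumulative incidence by arm and a subdistribution hazard ratio. For ICU stay the competing event is death in the ICU; for hospital stay it is death in hospital.
2. Keep the planned Mann–Whitney test and rank those deaths, tied, as the longest stay.

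Under either route, show survivors' stay descriptively beside mortality, without a test.

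The cost is wording and standard software, with no new data and no extra patients. The downside is that the result is a ratio or a rank instead of a difference in days, and the rank version mixes stay with mortality, which the report should say. At manuscript submission no participant had been enrolled and no interim analysis is planned, so the rule can be fixed before outcome data are examined.

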Indirect calorimetry is limited in specific clinical situations, such as patients with chronic obstructive pulmonary disease, high levels of positive end-expiratory pressure, or high inspired oxygen fractions. However, it is considered the most accurate method for estimating energy expenditure in mechanically ventilated ICU patients and is therefore used whenever technically feasible. These limitations are acknowledged, and measurements will be interpreted in the context of the patient’s clinical condition. For patients receiving ECMO, REE will be estimated as 20 kcal/kg because indirect calorimetry is less reliable in this setting [9].

Renal function will be monitored daily during the intervention period using serum creatinine levels, urine output, and blood urea nitrogen.

The type and volume of enteral nutrition administered are routinely documented in the electronic medical records and daily temperature charts as part of standard ICU care. Actual daily protein intake will be calculated from these records to assess adherence to the assigned protein and calorie target. Adjustments to protein delivery may be made by the attending physician based on clinical conditions such as intolerance or renal deterioration; the actual delivered protein dose will be documented and analyzed.

Details of how nutrition delivery, mobilization, and safety parameters are routinely monitored and documented as part of standard ICU care are summarized in Table 1.

**Table 1 Tab1:** Routine monitoring and documentation of nutrition delivery, mobilization, and safety parameters

Domain	What is monitored	How it is documented	Clinical oversight
Protein delivery	Daily protein intake (g/kg/day)	Electronic medical record (nutrition orders and intake records)	Adjusted by attending physician based on clinical condition
Energy delivery	Daily caloric intake (kcal/kg/day)	Electronic medical record / nutrition chart	Managed as part of routine ICU care
Mobilization	Frequency and type of mobilization sessions	Physical therapy and nursing notes in the medical record	Conducted according to patient tolerance

Protein tolerance and gastrointestinal intolerance (e.g., vomiting, diarrhea, abdominal distension, or interruption of enteral feeding) are routinely assessed and documented as part of standard ICU nursing and medical records.

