### Data collection

Baseline characteristics will be collected at the start of the intervention, and will include demographic and clinical data: age, sex, body mass index, primary diagnosis, and comorbidities assessed using the Charlson Comorbidity Index [26]. Severity of illness will be measured using the Acute Physiology and Chronic Health Evaluation (APACHE) II score. Additional clinical variables will include the presence of acute kidney injury (AKI) according to the Kidney Disease: Improving Global Outcomes criteria [27], presence of diabetes, score on the Malnutrition Universal Screening Tool [28], and the presence of malnutrition defined by the Global Leadership Initiative on Malnutrition criteria [29]. Furthermore, body composition will be assessed at enrollment using a bioelectrical impedance analyzer (InBody BWA2.0S; InBody Japan, Tokyo, Japan) to determine parameters including skeletal muscle mass, skeletal muscle index, fat-free mass index, and phase angle. Baseline FIM scores will not be collected because most patients are unable to undergo functional assessment at ICU admission due to sedation, mechanical ventilation, or impaired consciousness. Therefore, FIM was assessed only at hospital discharge, consistent with the study objective of evaluating post-ICU functional recovery.

Nutritional data will include the number of days from admission to initiation of enteral nutrition, the number of days until the target protein dose was achieved, and the mean intake of caloric, protein, parenteral caloric, enteral caloric, parenteral amino acid, and enteral protein during the intervention period. These data will be analyzed separately for Days 0–1 and from Day 3 onward.

Rehabilitation-related data will include the number of days from admission to initiation of mobilization, number of days mobilization was performed, and the ICU Mobility Scale score at ICU discharge [30].

In addition, treatment-related data will include the use of renal replacement therapy, use of ECMO, and the duration of mechanical ventilation.

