For all analyses, missing data will be addressed under the assumption of missing at random using multiple imputation. Given the possibility of non-random loss to follow-up after hospital discharge, sensitivity analyses exploring departures from the missing-at-random assumption (e.g., pattern-mixture or delta-adjustment approaches) will be conducted, and the extent and patterns of missingness will be reported. Variables related to missingness or outcomes—including group allocation, age, sex, Glasgow Coma Scale, ICU length of stay, and APACHE II score—will be incorporated in the imputation model. The specification of the imputation model will be informed by assessment of missing data patterns and inter-variable associations to ensure model adequacy. This approach will also be applied to post-discharge follow-up outcomes, including those assessed at 60 days, to account for missing data due to transfer or loss of contact.

Model assumptions for ANCOVA will be evaluated using standard diagnostic procedures, including inspection of residual distributions and assessment of homoscedasticity. If major violations are identified, appropriate transformations or robust alternatives will be considered and reported.

No interim analyses will be conducted. All statistical analyses will be performed using R (version 4.5.0), and all statistical tests will be two-sided. Statistical significance will be set at 0.05 across all analyses.

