This study is designed as a participant- and assessor-blinded randomized controlled trial, in which patients will remain blinded, while outcome assessors will also be blinded to group allocation to ensure reliability of the results. Another notable feature is the use of individualized caloric prescriptions based on REE measured through indirect calorimetry. This approach minimizes the risk of metabolic complications associated with overfeeding while ensuring appropriate nutritional management. Moreover, by balancing caloric targets with protein goals and employing an automated VBA-based calculation tool to determine formula and supplemental products, the study will enhance both precision and reproducibility in nutrition planning.

Several potential limitations should also be acknowledged. First, this is a single-center study, which may limit the generalizability of the findings. The single-site design was chosen for practical reasons, as relatively few ICUs are currently equipped with MPL, and its use requires specialized training. Second, the participant- and assessor-blinded design cannot completely eliminate the risk of treatment bias. To mitigate this concern, assessor blinding has been incorporated to minimize potential bias in outcome evaluation. Third, the duration of the intervention may vary among patients, with longer exposure potentially leading to greater functional improvement. To address this, ANCOVA including intervention duration as a covariate will be performed, and planned subgroup analyses will further account for potential heterogeneity.

Although recent post-hoc analyses have suggested potential harm of higher protein intake in patients with severe AKI [13], current guidelines do not recommend routine protein restriction.

Our protocol incorporates daily renal monitoring, predefined safety-driven adjustments, and planned subgroup analyses to address this concern.

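### The two named renal safety outcomes cannot isolate kidney injury that arises during the intervention, although creatinine and urine output are already monitored daily

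*Protocol article*

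**What the plan says.** All references are to the protocol article.

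- **Outcome** names the safety measures, beginning with the two renal ones: "Safety outcomes will include serum creatinine level at hospital discharge, maximum blood urea nitrogen level during the intervention". The section ranks none of them. It lists mortality among the secondary outcomes at hospital discharge.
- **Outcome** also gives rules for patients who die: minimum values for the two FIM scores, and for the others "the MRC score will be assigned as 0, and the BPI will be recorded as missing". Creatinine has no such rule.
- **Nutrition protocol**: "Renal function will be monitored daily during the intervention period using serum creatinine levels, urine output, and blood urea nitrogen".
- **Data collection**, among the variables taken at the start of the intervention: "Additional clinical variables will include the presence of acute kidney injury (AKI) according to the Kidney Disease: Improving Global Outcomes criteria". RRT use is collected as treatment-related data.
- **Statistical analyses** and **Subgroup analysis** use AKI and RRT as adjustment and subgroup factors, not as outcomes.
- **Statistical analyses**, on missing data: "For all analyses, missing data will be addressed under the assumption of missing at random using multiple imputation".
- **Interventions**: the core period runs from Day 3 until the patient leaves the ICU, dies or starts oral intake, with a cap of 28 days after randomisation.
- **Discussion**: "recent post-hoc analyses have suggested potential harm of higher protein intake in patients with severe AKI". Daily renal monitoring is offered as part of the answer.

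**The concern.** The protocol identifies a renal hazard of the higher dose, enrols patients who already have AKI, and says that daily monitoring addresses the hazard. The outcomes it then names do not use most of that monitoring.

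Creatinine is read once, at hospital discharge. That may be well after exposure has ended, it is available only in patients discharged alive, and it is silent on AKI that came and went. Maximum BUN has the right time window. But urea production follows protein intake, so a higher maximum in the high-protein arm is expected whether or not the kidney is harmed. This is a physiological point and the article does not discuss it.

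There is no independent monitoring board (Design and settings) and no interim analysis (Statistical analyses), so the final comparison between arms carries much of the weight. With the two named measures, the trial could report similar discharge creatinine and an ambiguous BUN difference while one arm had more AKI during treatment.

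**Working it through.** **1. The plan's own figure.** No figure is given for any renal outcome, so the only one to reproduce is the sample size. With a difference of 17, SD 20, two-sided α 0.05 and power 0.95 (printed as β), the normal approximation gives 2 × (1.960 + 1.645)² × 20² / 17² = 35.97, so 36 per arm. The exact t-test has power 0.945 at 36 and 0.950 at 37, so the stated 37 is right. For 15% dropout, 37 / 0.85 = 43.5, so 44 per arm or 88; the plan uses 90. This point does not affect the sample size. It fixes the denominator at 90, or 45 per arm.

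**2. What each measure can show.**

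| Measure | Covers the intervention? | Exists for in-hospital deaths? | Separates injury from protein dose? | Named as an outcome? |
|---|---|---|---|---|
| Creatinine at hospital discharge | No, one later value | No | Yes, but only for injury still present | Yes |
| Maximum BUN | Yes | Yes | No | Yes |
| Peak creatinine, highest KDIGO stage | Yes, from daily values | Yes | Yes | No |
| New RRT | Yes | Yes | Yes | No (RRT use is collected) |

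**3. Patients without a discharge creatinine.** The article gives no mortality rate. At an assumed in-hospital mortality of 10%, 20%, 30% or 40%, the number is 90 × 0.10 = 9, 90 × 0.20 = 18, 90 × 0.30 = 27 or 90 × 0.40 = 36.

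**4. Illustration of lost sensitivity.** Every rate here is an assumption: incident AKI 30% versus 50%; unresolved AKI doubles creatinine; SD of log creatinine 0.35; mortality 40% with AKI and 15% without; t-test on log creatinine in survivors; 45 per arm; 4,000 simulated trials.

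AKI among survivors is 0.3 × 0.60 / (0.3 × 0.60 + 0.7 × 0.85) = 0.18 / 0.775 = 0.232 in one arm and 0.5 × 0.60 / (0.5 × 0.60 + 0.5 × 0.85) = 0.30 / 0.725 = 0.414 in the other. If none resolves, the expected ratio of geometric means is exp[(0.414 − 0.232) × ln 2] = 1.13, which agrees with the simulation.

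| AKI resolved by discharge | Ratio of geometric means | Power, discharge creatinine (with deaths) | Power if nobody died |
|---|---|---|---|
| 0% | 1.13 | 0.19 | 0.28 |
| 50% | 1.07 | 0.09 | 0.11 |
| 80% | 1.03 | 0.06 | 0.06 |
| 100% | 1.00 | 0.05 | 0.05 |

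The ratios are those with deaths. A comparison of incident AKI itself has power of about 0.49 throughout. Resolution does most of the damage; deaths add to it when AKI persists.

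**5. Precision of the added outcomes.** For 30% versus 50% with 45 per arm, the standard error of the risk difference is √(0.3 × 0.7/45 + 0.5 × 0.5/45) = 0.101. The 95% interval is 20 ± 1.96 × 10.1 points, or about 0 to 40. For a 10-point difference (20% versus 30%, or 30% versus 40%), power is only 0.19 or 0.17.

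**The case against.** The strongest reply is that renal safety does not rest on one late value. Outcome lists two renal markers, and maximum BUN spans the intervention. Mortality is compared between arms, RRT use is collected and could be tabulated, and Design and settings provides adverse-event monitoring, periodic review by the principal investigator and reporting of serious events to the ethics committee. The safety list is introduced as what will be included, so it may not be complete. All of this stands, and it makes the coverage partial rather than absent. It does not repair the gap: BUN is confounded with the dose under test, mortality does not identify a renal cause, and the stated creatinine time point does not fit the stated hazard.

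Three stronger readings are tempting, and the article does not support them.

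- A reader might infer that discharge creatinine is the main renal outcome. The article ranks no safety outcome.
- A reader might infer that creatinine will be imputed for the dead. The imputation rule covers all analyses, and creatinine has no death rule, so a literal reading leads there. But the article never says so for creatinine, and an analysis plan that is not shown may settle it. The planned check on the missing-at-random assumption is motivated by later loss, "Given the possibility of non-random loss to follow-up after hospital discharge, sensitivity analyses exploring departures from the missing-at-random assumption", so it does not clearly reach in-hospital deaths.
- A reader might infer that an excess of deaths in one arm could go unseen. The mortality comparison would show it, though not its cause.

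It is also fair that the added outcomes would not be powered, and that daily creatinine and urine output are described as monitored but are absent from the Data collection list.

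**Conclusion.** The point holds as a poor choice of stated measures, not as missing detail. The protocol raises a renal hazard, has the daily values that bear on it, and names one outcome that cannot show resolved AKI and another that rises with the dose. Incident or worsened AKI, peak creatinine and new RRT are not outcomes anywhere in the article.

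The size cannot be taken from the article, which gives no rates for mortality, AKI or resolution. Under the assumptions above, a 20-point excess in AKI leaves discharge creatinine with power between 0.19 and the 5% error rate, depending on how much AKI resolves, and 9 to 36 of 90 patients have no discharge value at 10–40% mortality. Those figures show direction and scale and are not predictions. The primary analysis and the sample size are unaffected. It should be corrected, but it does not invalidate the trial.

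**What to change.** In the Outcome section, add to the safety outcomes:

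- peak creatinine and highest KDIGO stage from Day 3 to the end of the intervention;
- new or worsened AKI relative to status at enrolment;
- new RRT.

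Report the event outcomes by arm as counts and risk differences with confidence intervals, with deaths alongside, overall and by AKI at enrolment. Summarise peak creatinine by arm in the same table. Keep maximum BUN, read with the dose difference in mind, and keep discharge creatinine as a descriptive figure in survivors. In Statistical analyses, state that the imputation rule does not apply to discharge laboratory values of patients who died.

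The cost is small: daily creatinine and urine output must be added to the Data collection list and extracted from the record, and a reference creatinine for AKI must be defined, which the article does not yet do. No extra tests or visits are needed, and 90 patients remains the target. The results should be presented as estimates, because the trial is not powered for them. Trial status says that nobody had been enrolled at submission; the change should in any case be made before any comparison by arm is seen.
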